## Methods

### Study Design

A pilot community-based mixed methods design is used to assess the feasibility and effectiveness of the WE2CARE program. WE2CARE involves two sequential phases: a quantitative component that includes a waitlist randomized controlled trial and a qualitative component that involves focus groups. The waitlist control group will be used as an untreated comparison for the active experimental group to determine if the program had an effect.

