### Data Collection

Informed consent will be obtained prior to data collection. Data will be gathered using both quantitative and qualitative tools, which include self-completed questionnaires and focus groups.

Quantitative data will be captured for participants in the control and intervention groups through self-report instruments that will be administered online pre- and postintervention. The intervention group will also complete the questionnaires 6 weeks postintervention. The survey questionnaires will include the following:

1. The preintervention survey will include sociodemographic and health-related questions.

2. The standardized scales administered preintervention, postintervention, and at the 6-week follow-up will include the following:

The Depression, Anxiety and Stress Scale (DASS-21), a set of three self-report scales (21 items) designed to measure the emotional states of depression, anxiety, and stress.The Acceptance and Action Questionnaire (AAQ-2), a 7-item scale specifically designed to measure the impact of ACT core processes conceptualized as psychological flexibility.The Cognitive and Affective Mindfulness Scale – Revised (CAMS-R), a 12-item measure designed to capture a broad conceptualization of mindfulness not specific to any particular type of meditation training.The Multi-System Model of Resilience Inventory (MSMR-I), which consists of three subscales: internal resilience, pursuits and coping, and external resilience. Each subscale contains 9 self-reported items and indicates where the barriers to one’s resilience lie. These scales have shown good psychometric properties including internal consistency, test-retest reliability, and validity.

3. Participants’ evaluation of the WE2CARE program. Participants’ feedback about the program will be captured through a 12-item questionnaire that elicited their perceptions of the impact the program had on their mental and social well-being and their knowledge of how to access mental health services.

Qualitative data will be obtained through focus groups and interactive entries embedded throughout the 6 online modules, including questions on caregiving burden and factors that promote resilience in Module 1 and weekly valued action data logs on self-care in Modules 2-6.

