### Data Analysis Planning

Descriptive statistics will be used to summarize participants’ sociodemographics, self-reported health characteristics, and practices. Both independent and dependent *t* tests will be performed to assess the mean score differences for each outcome measure across and within groups. An independent *t* test will be used to compare mean scores across the intervention and control groups. Paired *t* tests will be used to compare the following: (1) baseline and postintervention outcomes and (2) baseline and 6-week postintervention outcomes among intervention participants.

The number of intervention participants at low risk and at risk for anxiety, depression, and stress will also be compared at baseline, postintervention, and 6 weeks postintervention. The Fisher exact test will be used to determine if the number of intervention participants at risk for anxiety, depression, and stress changed across time. Risk for anxiety, depression, and stress will be assessed using the DASS-21 and AAQ-7. The DASS-21 contains three subscales that assess anxiety, depression, and stress. Those that score at a moderate severity level or above for anxiety, depression, and stress will be considered at risk. The cutoffs for a moderate severity level will be set at 9 for anxiety, 13 for depression, and 18 for stress. Based on the AAQ-7 scoring instructions, a score above 23 is associated with depression or anxiety symptoms.

Linear mixed effects models will be created for each outcome of interest from baseline to postintervention among participants in the intervention and control groups. Each model will include two fixed effects parameters and two random effects parameters, one for the intercept and one for the outcome. The intercept fixed effect represents the typical initial score of an outcome and the outcome fixed effect represents the typical increase or decrease in score from baseline to postintervention.

Participants’ feedback on the 12-item questionnaire will be stratified by study arm allocation and an independent *t* test will be used to determine if there are differences in survey responses by study arm allocation.

Quantitative data will be analyzed using SPSS (version 27; IBM Corp) and R (version 1.2.5003; R Foundation for Statistical Computing) for Windows. A threshold of .05 will be used to determine the level of significance for all *P* values.

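### Fisher's exact test is planned for change over time in the at-risk status of the same intervention women; a paired test is needed, and the result should be labelled as uncontrolled within-arm change.

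*Protocol article*

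**What the plan says.** The Data Analysis Planning section of the protocol article turns the DASS-21 into a binary status: "Those that score at a moderate severity level or above for anxiety, depression, and stress will be considered at risk". It adds a cutoff on the acceptance and action questionnaire. The quantity analysed is given as "The number of intervention participants at low risk and at risk for anxiety, depression, and stress". On timing, the section says that these counts "will also be compared at baseline, postintervention, and 6 weeks postintervention". The test is then named: "The Fisher exact test will be used to determine if the number of intervention participants at risk for anxiety, depression, and stress changed" over that period.

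Three other statements bear on the point.

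- The paragraph before it, in the same section, plans paired t tests for the intervention participants' scores (baseline v postintervention, baseline v 6 weeks).
- That paragraph also plans an independent t "test will be used to compare mean scores across the intervention and control groups".
- Data Collection sets the timetable: "Quantitative data will be captured for participants in the control and intervention groups through self-report instruments that will be administered online pre- and postintervention". For the later visit it says only: "The intervention group will also complete the questionnaires 6 weeks postintervention".

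Study Design gives the purpose of the controls: "The waitlist control group will be used as an untreated comparison for the active experimental group to determine if the program had an effect".

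**The concern.** Fisher's exact test compares independent groups. Here the groups are time points, and each woman appears at every one, so 17 women would be counted as 34 observations (two times) or 51 (three times), and the information on who changed would be discarded. The section recognises the pairing for the scores but not for the statuses derived from them.

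The P value may therefore not be valid for the question asked, at the .05 threshold that the section sets for all P values. The analysis also covers one arm only, so even a correct P value would describe change over time and not an effect of the programme.

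**Working it through.** The article gives no expected at-risk rate, correlation or power for this analysis, so there is no figure of its own to reproduce.

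**Inputs**

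- From the article: 17 intervention and 12 control completers (Results); threshold .05, taken as two-sided (Data Analysis Planning).
- Assumed: all at-risk rates, and the within-person correlation phi.

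**1. Which table would the test be run on?**

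- *Time by risk status.* The rows are the same women, so independence fails. The variance of the change in proportion is [p0(1−p0) + p1(1−p1) − 2·cov]/n, and Fisher's test behaves as if cov = 0. At p0 = p1 = 0.5 and phi = 0.5, the paired variance is (0.25 + 0.25 − 0.25)/17 = 0.25/17, against 0.50/17 under independence. The planned test assumes twice the true variance.
- *Baseline status by follow-up status.* This tests association. If 6 women stay at risk, 11 stay at low risk and nobody changes, Fisher gives P = 1/C(17,6) = 1/12,376 = 0.00008, although there is no change at all.

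Neither reading answers the stated question.

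**2. Example: 12 of 17 at risk falls to 6 of 17**

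- Fisher, time by status: the table probabilities are C(17,k)·C(17,18−k)/C(34,18). Summing both tails (k ≤ 6 and k ≥ 12) gives 2 × (0.03475 + 0.00668 + 0.00073 + 0.00004) = 0.084.
- Exact McNemar, six improved and none worsened: 2 × (1/2)^6 = 0.031.
- Exact McNemar, seven improved and one worsened (same totals): 2 × (1 + 8)/2^8 = 18/256 = 0.070.

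Fisher gives 0.084 in both cases because it sees only the totals. The conclusion differs in the first case and agrees in the second.

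**3. Power, n = 17, assumed fall from 70% to 37%**

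P(at risk both times) = p0·p1 + phi·√[p0(1−p0)p1(1−p1)] = 0.259 + 0.221·phi. The other cells follow by subtraction. Rejection rates come from exact enumeration of the paired table.

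| phi | improve | worsen | Fisher | exact McNemar |
|---|---|---|---|---|
| 0 | 0.441 | 0.111 | 0.38 | 0.34 |
| 0.2 | 0.397 | 0.067 | 0.36 | 0.39 |
| 0.4 | 0.352 | 0.022 | 0.34 | 0.47 |

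The largest phi that these rates allow is (0.37 − 0.259)/0.221 = 0.50, so the last row is near the favourable end for McNemar.

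**4. Size under no change, 50% at risk at both times, n = 17**

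| phi | Fisher | exact McNemar |
|---|---|---|
| 0 | 2.4% | 2.1% |
| 0.3 | 0.73% | 1.29% |
| 0.5 | 0.18% | 0.57% |

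Both fall far below 5%. Exact McNemar needs at least six changes, all one way, to reach .05 (five give 2 × (1/2)^5 = 0.0625), so much of the shortfall comes from the small sample.

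**5. What a within-arm test can show**

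Suppose both arms drift from 70% to 40% at risk with no programme effect (assumed). Over phi 0 to 0.5, the intervention-arm test is significant in 31% falling to 24% of trials with Fisher, and in 27% rising to 40% with McNemar. A between-arm Fisher test at postintervention, 17 v 12 women, rejects in 2.9%. A paired test alone does not turn change over time into a treatment effect.

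**The case against.** The case for leaving the plan alone is that the at-risk count is an extra analysis in a pilot. The same scores, before they are dichotomised, receive correctly paired t tests. The error under positive correlation is conservative, so it does not create false claims. With 17 women either test often misses the assumed shift: McNemar reaches only 0.47 in a favourable setting, and at phi 0 it has less power than Fisher. All of this stands and lowers the severity. None of it makes the named test suitable, and nothing else in the article corrects it.

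A reader might draw three stronger conclusions, which the article does not support.

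- *The plan gives no treated-versus-control answer.* This is true of the at-risk counts only. The section compares mean scores for each outcome measure between arms by independent t test, and those measures include the scales that define risk.
- *Regression to the mean will lower the at-risk count.* The inclusion criteria set no distress threshold, so women are not selected for high baseline scores. Without such selection, regression moves women across a cutoff in both directions. Self-selection while distressed is possible but not shown. An ordinary time trend is the sounder reason for caution.
- *The test inflates false positives.* On the time-by-status table with positive correlation it does the opposite (step 4).

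**Conclusion.** The point holds for the choice of test. Fisher's exact test does not suit change over time in the same women on either reading of the table, and the section is inconsistent with its own paired t tests.

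The size depends on within-person correlation. The power difference (McNemar minus Fisher) runs from −0.04 at phi 0 to +0.13 at phi 0.4 for the assumed fall from 70% to 37%. A result can cross .05, as in the example where nobody worsens, but need not. Positive correlation is expected for repeat scores on one scale, but the article gives no value, and all rates and phi here are assumptions.

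The one-arm restriction limits what the result can mean. It is not a gap in the trial as a whole, because the between-arm question is asked on the mean scores. Severity is moderate. A reader might rate it as critical, but a supplementary analysis in a pilot, with an error that is conservative under positive correlation, does not support that.

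**What to change.** Replace Fisher's exact test for change over time with exact McNemar tests (baseline v postintervention, baseline v 6 weeks), or with Cochran's Q over the three times. Report the numbers improved and worsened beside each P value.

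Label the result as uncontrolled change within the intervention arm, which cannot separate programme effect from time trend.

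If a claim of effect is to be made on at-risk status, compare it between arms at postintervention, taking baseline status into account. Fisher's test is valid across arms because the women are different, although unadjusted power is about 0.30 for an assumed 30% v 60% at 17 v 12. No such comparison is supported at 6 weeks, where Data Collection states questionnaires for the intervention group only.

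The cost is a few lines of text, with the same data and software. The article says analysis is still in progress, so the change should be recorded with its date and with whether results had been seen.

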### Participants and Recruitment Strategies

A total of 36 participants will be recruited by two community champions (ie, trusted members of the caregivers’ community collaborating with community health organizations serving the TFW population) and a snowball sampling technique. The inclusion criteria will include the following: (1) female adults aged ≥18 years, (2) residing in the Greater Toronto Area, (3) working on a temporary work permit as live-in caregivers, (4) able to speak and read English, (5) have internet access, and (6) able to take part in the 6-week intervention. They will be randomized to either the intervention arm or control arm using a random number generator.

In Phase 2 of our study, we will conduct two focus groups with a subset of participants from Phase 1 who indicate interest in participating. The aim of the focus groups is to gain a deeper understanding about participants’ views of the effectiveness of WE2CARE in promoting mental health, their perceived barriers and challenges in accessing this method of delivery (ie, online), and their recommendations to improve the content and method of delivery of this program.

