## Results

The WE2CARE study protocol has been approved by the research ethics boards of Ryerson University (REB 2019-036) and the University of Toronto (RIS37623). Data collection occurred between November 2019 and May 2020. Of 18 participants in the intervention group, one did not complete the baseline questionnaire, while 6 of 18 participants in the control group withdrew from the study due to other competing life priorities. The total number of participants who completed the study was 29, with 17 in the intervention group and 12 in the control group. Our intervention group was divided into two cohorts of 9 and 8 participants, respectively. This allowed more opportunity for participants to share their experiences, mental health stressors, and application of ACT strategies during weekly videoconferences. The control group received the intervention after the two intervention cohorts were completed. Data analysis is in progress and results will be published in 2021.

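### Two scores per woman cannot support a correlated random intercept and random change with a free residual; the mean change survives, the variance components do not

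*Protocol article*

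**What the plan says.** Data Analysis Planning sets the scope of the models: "Linear mixed effects models will be created for each outcome of interest from baseline to postintervention among participants in the intervention and control groups". It then fixes their content: "Each model will include two fixed effects parameters and two random effects parameters, one for the intercept and one for the outcome". It explains the second effect by saying that "the outcome fixed effect represents the typical increase or decrease in score from baseline to postintervention", so the second random effect is a woman-specific change over time. The intercept is described as the usual starting score, which implies that baseline is coded 0 and postintervention 1.

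The section does not say whether the two random effects are correlated, and it puts no constraint on the residual variance. It names SPSS and R as software, with no R package.

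Data Collection confirms two occasions for both arms, through "self-report instruments that will be administered online pre- and postintervention". The third occasion belongs to one arm: "The intervention group will also complete the questionnaires 6 weeks postintervention".

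On numbers, "A total of 36 participants will be recruited", and the Results section reports: "The total number of participants who completed the study was 29, with 17 in the intervention group and 12 in the control group".

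**The concern.** A random intercept lets women differ in level, a random change lets them differ in response, and the residual takes up what is left. Separating individual differences in change from residual noise needs more than one change per woman. Two scores give one change each, so the data cannot show how much of its spread is true variation in response and how much is noise.

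Three things are at stake. Reported variance components or woman-specific changes could be arbitrary. The fit could stop, depending on the software. The analyst would then have to choose another structure after seeing the data, and the same choice arises for every outcome.

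**Working it through.** The article gives no figure for this model, so there is nothing to reproduce. The check counts parameters and then looks at trial fits.

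**Inputs.** From the article: two occasions per woman; a random intercept and a random change; 36 planned and 29 completers (17 and 12). Assumed because not stated: a free residual variance and, for steps 1 to 4, a free covariance between the random effects.

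**Step 1: count.** Let t0 be the intercept variance, t1 the change variance, t01 their covariance and s the residual variance. With time coded 0/1:

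- baseline variance V11 = t0 + s
- covariance V12 = t0 + t01
- postintervention variance V22 = t0 + 2·t01 + t1 + s

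There are four unknowns and three equations (rank 3 of 4), so the four cannot be recovered.

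**Step 2: example.** These three admissible sets imply the same covariance matrix:

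| t0 | t01 | t1 | s | V11 | V12 | V22 |
|---|---|---|---|---|---|---|
| 60 | 0 | 20 | 40 | 100 | 60 | 120 |
| 70 | -10 | 40 | 30 | 100 | 60 | 120 |
| 80 | -20 | 60 | 20 | 100 | 60 | 120 |

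The change variance runs from 20 to 60, and no data could tell the sets apart.

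**Step 3: what survives.** The variance of an observed change is V11 + V22 - 2·V12 = t1 + 2s. In the three sets this is 20 + 80, 40 + 60 and 60 + 40, each 100. With 29 complete pairs the standard error of the mean change is sqrt(100/29) = 1.857 in every case.

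**Step 4: trial fits.** Data were simulated for 29 women with assumed variances 64 and 70 and covariance 40.

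- In one data set, residual variances of 0.1, 5, 10 and 15 gave the same -2 REML kernel (262.182) and the same standard error of the mean change (1.1707), equal to the paired value.
- In a second data set, lme4 with correlated effects stopped: 29 × 2 = 58 observations against 29 × 2 = 58 random effects.
- On those same data nlme returned t0 = 79.83, t1 = 35.34, s = 11.48, with an interval for the residual SD from about 5e-16 to 2e+16. The uncorrelated model returned 68.79, 13.26 and 22.52. Both give V11 = 91.31 and t1 + 2s = 58.30, hence a standard error of sqrt(58.30/29) = 1.418, equal to the paired analysis. The mean change was -5.506 in both.

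The tie between observations and random effects does not depend on sample size: 36 women give 72 and 72; the arms fitted separately give 34 and 34, and 24 and 24. If the 6 withdrawn controls had baseline scores (an assumption), the count would be 58 + 6 = 64 observations for 2 × 35 = 70 random effects.

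**Step 5: covariance set to zero.** Then t0 = V12, s = V11 - V12 and t1 = V22 - V11: three parameters, rank 3 of 3, just identified. Since t1 cannot be negative, V22 must be at least V11. In simulations with n = 29, an assumed baseline variance of 64 and a correlation of 0.6, the unconstrained solution fell outside the permitted range in about 78%, 50% and 27% of data sets, for true post/pre variance ratios of 0.8, 1.0 and 1.25.

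**Step 6: the 6-week score.** With three occasions the correlated model is identified (rank 4 of 4), but only the intervention arm has the third score. The control arm still has two.

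**The case against.** The text names two random effects and no covariance. Read literally, as two variances and a residual, the model is just identified, and both lme4 and nlme fitted it. It also does not break down when the postintervention variance is the smaller one: the change variance goes to zero and the model becomes a random intercept model. In 400 simulated data sets with complete pairs (n = 29, true variance ratios from 0.6 to 1.25), the standard error of the mean change matched the paired value to within a relative 3e-8.

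The plan also gives meaning only to the fixed effects. It tests no variance component, and it plans independent and paired t tests that do not use this model. The covariance structure is a detail that a condensed article may leave to a fuller plan.

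Most of this stands, and it limits the point. A reader might infer that the model is unidentifiable on any reading, that it cannot be validly fitted, or that its estimate of the mean change is wrong. The documents support none of these. Nor do they show that the named software must fail: only lme4 stopped, only on the correlated form, and no SPSS fit was made.

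The objection does not remove the point. The two random effects are stated, not left open. One reading of that statement is over-parameterised. The other carries a variance restriction that the article neither mentions nor justifies.

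**Conclusion.** The point holds in a limited form. For two occasions per woman, the stated random-effects structure is either over-parameterised by one (four parameters for three quantities) or just identified under an unstated restriction on the variances. In the first case the variance components carry no information of their own and some software will refuse the fit.

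The severity is minor to moderate, because inference on the mean change survives. The exact agreement with the paired analysis rests on complete pairs. With incomplete records the mean change remains identified through the covariance matrix of the two scores, but restrictions on that matrix can then affect the estimate, which is a further reason to fix the structure in advance.

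The parameter count rests on the 0/1 time coding implied by the article and on a free residual variance. The simulation percentages rest on assumed variances and correlations and are only illustrative.

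**What to change.** In Data Analysis Planning, replace the two random effects with one of the following, the same for every outcome:

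- **Preferred:** no random effects and an unstructured 2x2 within-person covariance, fitted by REML with Kenward-Roger or Satterthwaite degrees of freedom. This has three parameters for three quantities and puts no restriction on how the two variances compare.
- **Simpler:** a random intercept only. This has two parameters and is identified, but it assumes equal variances at baseline and postintervention, and the text should say so.

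Do not keep the random change by adding the 6-week score to a model for both arms, since the controls lack that score. If a random change is kept for another reason, state the constraint that identifies it and do not interpret the variance components beyond it.

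The cost is one line of the analysis text, with no effect on data collection or operations.

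### The planned mixed models contain no arm or arm-by-time term, so they cannot estimate WE2CARE against the waitlist; that comparison rests on a t test alone

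*Protocol article*

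**What the plan says.** The Study Design section of the protocol article gives the control arm its purpose: "The waitlist control group will be used as an untreated comparison for the active experimental group to determine if the program had an effect".

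Data Analysis Planning then sets out the longitudinal model in three steps.

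- Population and period: "Linear mixed effects models will be created for each outcome of interest from baseline to postintervention among participants in the intervention and control groups".
- Parameters: "Each model will include two fixed effects parameters and two random effects parameters, one for the intercept and one for the outcome".
- Meaning of the two fixed effects: the intercept stands for the usual starting level on the scale. Of the second term the article writes that "the outcome fixed effect represents the typical increase or decrease in score from baseline to postintervention".

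The same section plans one comparison of outcome scores between arms: "An independent *t* test will be used to compare mean scores across the intervention and control groups". The other outcome tests compare time points. There are paired t tests, which for the follow-up use "baseline and 6-week postintervention outcomes among intervention participants", and Fisher exact tests on the number of intervention participants at risk over time. A further between-arm t test is planned, but on the programme-feedback questionnaire and not on the outcome scales.

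**The concern.** The count of fixed effects is closed at two and both are defined, so there is no room for an arm or arm-by-time term. This cannot be read as detail left to a fuller plan: the article states the model, counts its parameters and says what each one means.

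The mixed model is the only planned analysis that brings both arms and both time points together. That makes it the natural place to estimate how far change under WE2CARE differs from change on the waitlist, and as specified it cannot. Its change term responds to anything that moves scores in both arms, such as regression to the mean, season or repeat completion of the same scales. If the arms are pooled, it also shrinks a real programme effect towards the untreated change.

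**Working it through.** **Inputs from the protocol article.** Two fixed effects, both defined (Data Analysis Planning). Two time points, baseline and postintervention (same section). 36 women planned (Participants and Recruitment Strategies); 18 per arm, with 17 intervention and 12 control completers (Results). Significance threshold .05 (Data Analysis Planning).

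**Assumed inputs.** The article gives no SD, effect size, drift or correlation. The following are assumptions: SD 1 at each time point, pre-post correlation r = 0.5 to 0.7, a change of 0.8 SD in the intervention arm only, or a drift of 0.3 SD shared by both arms; two-sided test. There is no stated figure to reproduce.

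**Step 1. What the model contains.** As written, for woman i at time t (0 or 1), the mean score is b0 + b1·t. Here b0 is the typical initial score and b1 the typical change. Arm does not appear.

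**Step 2. One model over both arms.** In completers, b1 estimates

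(17/29) × change in intervention + (12/29) × change in control = 0.586 × change in intervention + 0.414 × change in control.

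This needs no assumption about SD or correlation.

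- Intervention 0.8 SD, control 0: 0.8 × 17/29 = 0.47 SD, against a true difference in change of 0.8 SD. With 18 per arm it would be 0.8 × 18/36 = 0.40 SD.
- Changes of -0.4 and +0.4 SD at 18 per arm: b1 has expectation 0, although the arms differ by 0.8 SD.

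**Step 3. False signal under shared drift, same reading.** The SD of a change score is √(2(1 − r)). With n = 29 the noncentrality is 0.3 × √29 / √(2(1 − r)), on 28 degrees of freedom, with critical value 2.048.

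| r | SD of change | Noncentrality | Probability that b1 is significant |
|---|---|---|---|
| 0.5 | 1.000 | 1.616 | 0.345 |
| 0.6 | 0.894 | 1.806 | 0.415 |
| 0.7 | 0.775 | 2.086 | 0.522 |

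Simulation of 6,000 trials per scenario gives 0.345, 0.413 and 0.517. Across the simulated drifts (0.3 and 0.5 SD), the test of the arm difference in change rejects in 0.047 to 0.055 of trials, as it should.

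**Step 4. One model per arm.** Each fit returns its own b1, a within-arm change. No parameter or test compares the two. A significant change in one arm and a non-significant change in the other is not a test of their difference. The figures in steps 2 and 3 do not apply to this reading.

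**Step 5. With arm-by-time added.** In simulations of a random-intercept model (300 runs per scenario, r = 0.5), the arm-by-time coefficient averaged -0.80 at 18/18 and -0.83 at 17/12 when the true difference was -0.80. When both arms improved by 0.80 SD, it averaged 0.00 and 0.02, with rejection rates of 3% and 6%.

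**Step 6. The random effects.** Two measurements per woman supply three second moments: two variances and one covariance. A random intercept, a random slope, their covariance and a residual are four parameters, so they cannot be separated. Forcing the two random effects to be uncorrelated brings the count to three, but then the later variance can only equal or exceed the earlier one. Adding arm terms alone would leave this problem in place.

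**The case against.** The strongest reply is that a between-arm analysis is planned. The independent t test covers each outcome measure, and if it is applied to postintervention scores, drift common to both arms does not bias it. This stands. A reader might infer from the mixed-model paragraph that the randomised comparison is never made; the article does not support that. What remains is that the t test's time point is not stated, and that the one model using both arms and both time points adds nothing to the comparison.

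A second reply is that the article describes the change term only as typical change. It never names that term as the programme effect, and no analysis is designated primary. This also stands. A reader might infer that the authors intend to claim effectiveness from it, but the text does not say so. Misreading is a risk, given that the models cover both arms and a .05 threshold applies to every P value, but the error itself is not written down.

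Third, the numbers hold only if the arms are pooled, and the effect, drift, SD and correlation are all assumed. The weights 17/29 and 12/29 are for completers; a mixed model that uses baseline scores from women who withdrew could weight the arms somewhat differently. All of this is right and limits the figures to illustration. It does not affect the absence of an arm term.

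Finally, this is a small pilot. But the Study Design section includes effectiveness among its aims, so a model fitted to both arms ought to address it.

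**Conclusion.** The model is wrong as written. With two defined fixed effects and no arm term, it cannot estimate WE2CARE against the waitlist, whether the arms are pooled or fitted separately. That conclusion follows from the text and needs no assumed values.

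The defect is confined to the mixed models. The only planned between-arm analysis of outcomes is therefore the independent t test, and the models do not serve the stated purpose of the waitlist arm. The illustrative size is a coefficient of about 0.47 SD for a true 0.8 SD difference, and about a 41% chance (35% to 52%) of a significant change term under a shared 0.3 SD drift. It rests on pooling, complete cases and the assumed values listed above.

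**What to change.** Specify each model as score = intercept + time + arm-by-time, with the arms' baseline means constrained equal because of randomisation; alternatively, add an arm main effect. Use a random intercept per participant and drop the random slope, since there are only two time points.

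Name the arm-by-time coefficient, with its 95% CI, as the model's estimate of the WE2CARE effect, and report it alongside the planned between-arm t test with that test's time point stated. Say that the time coefficient is not to be read as effectiveness.

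The cost is one extra fixed-effect parameter (two with the arm main effect), one random effect fewer, and a few sentences of text. No new data are needed, and the article reports that analysis is still under way.
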